**Intervention:**

**Group I :** Tablet Trikatu 1000 mg twice daily with luke warm water one hr after food for 12 weeks along with standard care (Statins)

**Group II:** Matching placebo 1000 mg twice daily with luke warm water one hr after food for 12 weeks along with standard care (Statins)

The participants in both groups will receive standard care as per the 2019 ACC/AHA

**Duration of intervention:** 12 weeks (84 days)

**Sample size:** 85 per group (Total 170)

**Study Population:** Patients with Dyslipidemia diagnosed based on the 2019 ACC/AHA Guideline on the Primary Prevention of Cardiovascular Disease.

## Background:

Lipid disorders involving derangements in serum cholesterol, triglycerides, or both are commonly encountered in clinical practice and often have implications for cardiovascular risk and overall health. Dyslipidaemias are collectively among the most commonly detected lifestyle or chronic metabolic disorder. They are classically characterized by abnormal serum levels of cholesterol, triglycerides, or both, involving abnormal levels of related lipoprotein speciesxiii. The most common risk factor and cause for mortality and morbidity associated with dyslipidaemia is associated atherosclerotic cardiovascular disease (ASCVD). Dyslipidemias are an active and expanding area of research, with recent studies providing insight into their molecular basis and genetic origins, outlining their role in the development of atherosclerosis, and clarifying the ability of pharmacologic agents to ameliorate ASCVD risk in affected individuals. There is a strong pathophysiological association of raised LDL cholesterol with initiation and progression of coronary atherosclerosis and contemporary clinical evidence shows that lowering its levels can regress and stabilize atherosclerotic vascular disease. Treatment of dyslipidaemia is the most effective modifiable target for improving cardiovascular outcomes.

In India, only limited studies exist on epidemiology of cholesterol and other lipoprotein lipids on large samples in the last 20 yearsxiv, xv. Studies from India have reported greater triglyceride levels in rural and urban populations associated with low HDL cholesterol levelsxvi. The low HDL cholesterol and hypertriglyceridemia are metabolically interlinked and their combination has been termed as atherogenic dyslipidemia, which is also associated with increased levels of small-dense LDL particles and insulin resistancexvii.

The prevalence rates of various fasting dyslipidemia in the first phase of ICMR INDIAB study restricted to urban and rural populations in 4 states in India was hypercholesterolemia in 13.9%, high triglycerides in 29.5%, low HDL cholesterol in 72.3% and high LDL cholesterol in 11.8%. 79% men and women had abnormalities in at least one of the lipid parametersxviii. Focus on dyslipidemia management is urgently required in India to halt the rising tide of coronary heart disease.

When lifestyle interventions alone are not enough to correct dyslipidemia, or those who are determined to be at sufficient ASCVD risk, lipid modifying drugs are used after a clinician-patient overall discussion. In most patients, currently available lipid modifying drugs are effective in bringing the lipid levels to goal thereby reducing the risk of CV events. The general approach to

management is that in young adult patients (20 - 39 years) promoting a healthy lifestyle can suffice and improve dyslipidemia. Pharmacological therapy in this population is usually indicated in patients with LDL-C levels (starting from 160 mg/dL or higher than 100 mg/dL in high risk patients).

Dietary interventions appear to be a promising strategy for managing premature hyperlipidemia. In a trial, a probiotic formulation resulted in decreased LDL-C and improvements in triglyceridemia and HDL cholesterol (HDL-C) levels. Mechanisms that support the potential efficacy of the abovementioned interventions include the suppression of liver cholesterol synthesis, reduction of intestinal cholesterol absorption and production of conjugated linoleic acid in the gutxix. Expanding scientific evidence indicates that the gut microbiota mediates pathophysiological mechanisms that alter lipid metabolism and other related metabolic traitsxx. Particularly, the intestinal microbiota has been recognized as a metabolically active endocrine organ of the human superorganism that can be a therapeutic target for hyperlipidemia and associated cardio-metabolic diseasesxxi.

"Trikatu"-an Ayurvedic formulation comprising of a 1:1:1 ratio of dried fruits of *Piper nigrum*, *Piper longum* and dried rhizomes of *Zingiber officinale* is widely used in Ayurveda clinical practice. In Ayurvedic Formulary of India it is used in various diseases like, Arocaka (Tastelessness), Agnimandya (Digestive impairment), Amadosa (Products of impaired digestion and metabolism / consequences of Ama), Gala Roga (Diseases of throat), Pinasa (Chronic rhinitis/sinusitis), Kustha (Diseases of skin), Swasa (Dyspnoea/Asthma), Kasa (Cough), Tvakroga (Skin disease), Gulma (Abdominal lump), Meha (Excessive flow of urine), Sthaulya (Obesity), Slipada (Filariasis)xxii. Clinical evidence from a study on Trikatu in dyslipidemia depicts statistically significant improvement in the parameters of lipid profile and obesity when administered for a period of 8 weeksxxiii.

This study is planned with the objective to utilize the anti-dyslipidemic activity of Trikatu to effectively improve the lipid metabolism and to regulate the gut dysbiosis which is now considered a marker of impaired metabolism

**Trial Design :** A randomized, double-blind, placebo-controlled clinical trial with a treatment period of 12 weeks.

#### **Summary of trial design:**

Eligible patients will be randomized into either the TK group or the placebo group. After screening, a total of 5 visits will be scheduled at baseline (visit 1) and Day 28(visit 2), Day 56 (visit 3), and

Day 84 (visit 4) to assess treatment efficacy and safety and a final without medication follow-up on Day 112 (Visit 5) to assess the sustenance of the response obtained (if any) in the trial participants.

### **Study objectives**

**Primary objective:** To assess the efficacy and safety of Ayurvedic Formulation "Trikatu" for improving lipid parameters in dyslipidemia

**Secondary Objective:** To assess the Changes in Gut Microbiota in response to the trial interventions and delineate correlates that predict favorable outcome in dyslipidemia patients

**Study setting:** Participants would be screened from the Department of Medicine, AIIMS, Bhubaneswar and Ayurveda OPD of Central Ayurveda Research Institute, Bhubaneswar. All investigations of the study subjects will be carried out at Biochemistry Department and Central laboratory, AIIMS, Bhubaneswar. All study procedures following enrollment will be done at AIIMS, Bhubaneswar. The gut microbiota analysis will be outsourced.

**Study Population:** Patients with Dyslipidaemia diagnosed based on the 2019 ACC/AHA Guideline on the Primary Prevention of Cardiovascular Disease and required for statin therapy will only be selected.

**Estimated Study Duration:** 2 years

- **Preparatory period:** 08 weeks
  - Recruitment of project personnel,
  - IEC approval
  - Preparation of CRF & e-Format
  - Training of personnel
  - Procurement of Medicines
- **Study intervention (for participants):** 12 weeks (84 days)
- **Follow-up:** 04 weeks
- **Recruitment period:** 60 weeks
- **Statistical analysis & Publication:** 12 weeks

### **Inclusion criteria:**

- Participants of any gender in the age group 25-60 years
- Diagnosis of moderate and high ASCVD risk dyslipidemia based on the ACC/AHA Guidelines, 2019 on the Primary Prevention of Cardiovascular Disease and indicated for statin therapy
- Body Mass Index (BMI)  $\geq 18.5$  and  $< 34.9$  kg/m^2.

- Written informed consent provided prior to screening, after receiving and understanding the subject information.
- Willingness to adhere to the treatment for a period of 12 weeks

#### **Exclusion criteria:**

- Subjects on any lipid altering drug therapy other than statins (including any contemporary, Ayurvedic or traditional medicines and nutritional supplements such as Omega-3 Fatty acids, anti-obesity drugs) within 4 weeks prior to screening†.
- Patients of dyslipidaemia with low ASCVD risk as per the ACC/AHA guidelines, 2019 and not indicated for statin therapy
- Subject using or were using the following medications: systemic corticosteroids, cyclical or non-continuous hormone therapy (estrogen or testosterone). within 6 weeks prior to screening
- Women who are pregnant or breastfeeding, or planning a pregnancy during the duration of the study.
- Smoker
- Diabetes mellitus, uncontrolled despite the use of anti-diabetic medication (HbA1c>9)
- Clinically significant liver and/or an elevation in either total bilirubin, alkaline phosphatase, AST, ALT of >2 times the laboratory reference
- Chronic kidney diseases having serum creatinine >1.2 mg%
- Diagnosis of acute myocardial infarction or cardiac arrest within previous 24 months.
- Musculoskeletal disease involving the lower limbs (severe painful arthritis, fracture, or joint contracture) which would impede the participant from adhering to the exercise regime.
- Uncontrolled hypertension defined as evidenced by a reproducible (repeated 5 minutes apart) sitting BP  $\geq 160$  systolic or  $\geq 100$  mmHg diastolic
- Co-morbid conditions that would interfere with study activities or response to treatment, which may include: Myopathies, Severe chronic pulmonary disease, thyroid disorders, endocrine diseases, Local, systemic acute or chronic infectious illness, cardiac arrhythmias, Neurological, psychological illness.
- Active substance abuse like alcohol or drug abuse in any form or history of alcohol/drug abuse or dependence within 6 months prior to study enrolment, or inability to refrain from alcohol use
- History or evidence of any other clinically significant disorder, condition or disease that, in the opinion of the investigator would interfere with the study evaluation, procedures, or completion.
- Any other condition, that as per the PI would jeopardize the study/ study outcomes

#### **Participant Enrolment:**

Before the participant begin participation in any study-specific activities/procedures, a copy of the ethics committee (IEC) approval of the protocol, informed consent, and all other participant

information and/or recruitment material, should be ready. All participants must personally sign and date the informed consent form before commencement of study-specific activities/procedures

A participant is considered enrolled when the investigator decides that the participant has met all eligibility criteria. The investigator is to document this decision and date, in the medical record and in/on the enrollment case report form (CRF).

Each participant who participates in the screening for the study receives an identification number before any study-related activities/procedures are performed. They shall also be assigned a unique enrolment number as soon as they are enrolled in the study. This number will be used to identify the participant throughout the clinical study and must be used on all study documentation related to that participant.

### **Participant information and consent**

Written, informed consent will be sought from all eligible participants.

If a participant was unable to give consent at trial entry, but regains capacity to receive information and give consent, he/she will be given information as soon as possible and asked whether he/she is willing to continue his/her participation in the trial. The participant and his/her legal representative will be informed of the right to withdraw from the trial and object to the use of his/her data. (Annex: Participant information sheet and Consent Form)

### **Participant Screening:**

Screened participants could broadly be defined as participants with dyslipidemia, who present at the site during the recruitment time interval. The willing volunteers will undergo a 1-2 hour screening with assessment of medical history, laboratory examinations, physical and ASCVD risk evaluation. The screening visit may be done over the course of more than one day, if needed, for participant convenience or due to delay in obtaining test results but it is preferable to finish it within one day.

### **Randomization procedure**

Block randomization list with unequal block sizes will be generated to randomize the participants to either receive intervention or a matching placebo in the ratio of 1:1. The packaging of the intervention and placebo will be done as per the randomization list and will maintain concealment and double blinded treatment allocation. After randomization neither the participant nor the investigator will be aware of the treatment allocation. Only the statistician who will generate the randomization sequence will be aware of the treatment allocation, and will keep the sequence sealed till the completion of the study.

### **Trial treatment:**

**Group I :** Tablet Trikatu 1000 mg twice daily with luke warm water one hr after food for 12 weeks along with standard care (Statins: dose/ intensity of Statins as per 2019 ACC/AHA Guideline)

**Group II:** Matching placebo 1000 mg twice daily with luke warm water one hr after food for 12 weeks along with standard care (Statins: dose/ intensity of Statins will be adjudicated as per 2019 ACC/AHA Guideline)

The participants (moderate and high-risk group) in both groups will receive standard therapy (Atorvastatin) as required and decided by the modern consultant who is part of the research team. The need/dosage/intensity for statins would be assessed through a baseline ASCVD risk assessment /2019 ACC/AHA Guideline on the Primary Prevention of Cardiovascular Disease and associated co-morbidities such as CVD, DM etc. A dosage of 20 mg and 40 mg Atorvastatin will be prescribed respectively to moderate and high risk study participants 30 minutes before dinner.

#### **Concomitant Therapy:**

The participant shall continue any concomitant therapy for DM or HTN or any other disease during the trial, which is not specifically excluded in the protocol. The investigators may prescribe any concomitant medications or treatments deemed necessary to provide adequate supportive care during the intervention period.

The therapy name, indication, dose, unit, frequency, start date, and stop date (if applicable) for all interventions (medicine/procedure/therapy) are to be recorded on each participant's CRF or Diary.

#### **Outcome Measures:**

##### **Primary Outcome Measure:**

- Change in fasting serum LDL cholesterol [ Time Frame: 0, 12 weeks ]

##### **Secondary Outcome measures:**

- Change in fasting Total cholesterol [ Time Frame: 0, 12 weeks ]
- Changes in the Gut microbiota profile (Time frame: 0, 12 weeks)
- Proportion of participants in the normal reference range (less than 200 mg/dl) for fasting T. cholesterol [ Time Frame: 12 weeks ]
- Change in fasting HDL-cholesterol [ Time Frame: 0, 12 weeks ]
- Change in fasting Triglycerides [ Time Frame: 0, 12 weeks ]
- Change in Adiponectin, ghrelin, apolipoprotein A1 and apolipoprotein B levels
- Change in Hs-CRP, tumor necrosis factor- $\alpha$  (TNF- $\alpha$ ) and interleukin-6 (IL-6)
- Change in Resting blood pressure (measured in triplicate) [ Time Frame: 0, 6, 12 weeks ]
- Change in fasting glucose & HbA1C [ Time Frame: 0, 12 weeks ]
- Change in fasting insulin [ Time Frame: 0, 12 weeks ]
- Improvement in homeostatic model assessment to quantify insulin resistance (HOMA-IR) [ Time Frame: 0, 12 weeks ]

- Drug compliance (elicited at each visit, in a structured compliance reporting form)
- Reported AE/ADR (Participant reported AE/ADR recorded in structured formats)

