#### Schedule of Assessments:

| Procedure                               | Screening visit | Baseline (Visit-1) (Day 1) | Day 28 (Visit-II) | Day 56 (Visit III) | Day 84 (Visit IV) | Day 112 (Visit V) Without medicine |
|-----------------------------------------|-----------------|----------------------------|-------------------|--------------------|-------------------|------------------------------------|
| Informed Consent                        | ✓               |                            |                   |                    |                   |                                    |
| Assessment of eligibility               | ✓               |                            |                   |                    |                   |                                    |
| Randomization                           | ✓               |                            |                   |                    |                   |                                    |
| Demographic data                        |                 | ✓                          |                   |                    |                   |                                    |
| History taking                          |                 | ✓                          |                   |                    |                   |                                    |
| Clinical examination, BP, Weight, waist |                 | ✓                          | ✓                 | ✓                  | ✓                 | ✓                                  |

|                                          |   |                           |   |   |   |   |
|------------------------------------------|---|---------------------------|---|---|---|---|
| circumference, BMI,                      |   |                           |   |   |   |   |
| Trial intervention                       |   | ✓                         | ✓ | ✓ | ✓ |   |
| ECG                                      | ✓ |                           |   |   |   | ✓ |
| TSH                                      |   |                           |   |   |   |   |
| HbA1C, Fasting Blood sugar               | ✓ |                           |   |   | ✓ |   |
| Hs-CRP, TNF- $\alpha$ & IL-6, HOMA-IR    |   | ✓                         |   |   | ✓ |   |
| Gut microbiota                           |   | ✓                         |   |   | ✓ |   |
| Lipid Profile                            | ✓ |                           | ✓ | ✓ | ✓ | ✓ |

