#### **Laboratory Investigations:**

All screening and on-study laboratory samples will be processed and sent to Biochemistry Department ,AIIMS, Bhubaneswar The results of this testing will be maintained in the source documents at the site. The date and time of sample collection will be recorded in the source documents at the site. At screening, laboratory investigations such as hematology (WBC, Hb, RBC, Hematocrit, Platelets, Differential Leucocyte Count), HbA1C, lipid profile, LFT, RFT, Thyroid profile would be done to rule out any systemic pathology, following which the participant would undergo an ECG. The results will be carried over to baseline and it is expected that the gap between screening and baseline visit is less than 2 days. Adiponectin, ghrelin, apolipoprotein A1 and apolipoprotein B, Hs-CRP, IL-6 would be assessed on baseline. Stool sample would be collected for

gut microbiome analysis at baseline and day 90. The laboratory investigations would again be done on day 90.

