### **Statistical analyses:**

A detailed Statistical Analysis Plan will be drawn up before breaking the randomisation code. We will analyse the data according to the intention-to-treat principle. Clinical outcome and laboratory outcome will be compared between the study groups by means of ordinal logistic regression, after adjustment for covariates.

We will perform pre-specified subgroup analyses of participants based on their risk as per the FRS, co-morbidities like DM, HTN, dose of standard care etc. Summary statistics by each treatment group will be tabulated at each visit. For continuous endpoints, the descriptive statistics include number of participants, mean, median, standard deviation, standard error, lower and upper quartiles, minimum, and maximum. For categorical endpoints, frequency, and percentage will be given. Missing data will not be imputed

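### Fasting insulin and HOMA-IR are outcomes for all participants although insulin-treated diabetes is eligible, and the protocol is inconsistent about when baseline glucose is drawn

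*Protocol*

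**What the plan says.** **Outcomes.** The Secondary Outcome measures include "Change in fasting insulin [ Time Frame: 0, 12 weeks" and "Improvement in homeostatic model assessment to quantify insulin resistance (HOMA-IR) [ Time Frame: 0, 12 weeks". Neither is limited by diabetes status or treatment.

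**Who can enrol.** The one exclusion that names diabetes is "Diabetes mellitus, uncontrolled despite the use of anti-diabetic medication (HbA1c>9". No antidiabetic drug is excluded.

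**Therapy during the trial.** Under Concomitant Therapy, "The participant shall continue any concomitant therapy for DM or HTN or any other disease during the trial", unless the protocol specifically excludes it. Investigators may add treatment for supportive care, and drug, dose and dates are recorded.

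**Diabetes is expected in the sample.** The Trial treatment section names it among the co-morbidities that bear on statin intensity. The Statistical analyses section plans subgroups by "co-morbidities like DM, HTN, dose of standard care etc".

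**Sampling.** In the Schedule of Assessments the row "HbA1C, Fasting Blood sugar" is ticked at screening and Day 84, and the row containing HOMA-IR at Day 1 and Day 84. The laboratory cost table follows the same split. Laboratory Investigations says of the screening tests that "The results will be carried over to baseline", with an expected gap of less than 2 days. The Day 1 list under Clinical visits, however, includes blood sugar among that day's fasting samples.

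**The concern.** HOMA-IR is fasting glucose multiplied by fasting insulin, divided by a constant. It is read as insulin resistance on the footing that the insulin is the participant's own. If some of it was injected, the product partly reflects a prescription. A change in injected dose between Day 1 and Day 84 could then register as better or worse insulin resistance when nothing of the kind has happened. Two listed secondary outcomes would mix interpretable and uninterpretable values.

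The sampling conflict raises a practical question: which glucose value enters the baseline index, and is insulin drawn at all? Missing data will not be imputed, so a missed baseline insulin sample removes that participant's change score for both outcomes.

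**Working it through.** The plan states no figure for this point, so the check is mainly textual. The arithmetic only sizes the consequences.

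**1. Can insulin users enrol?** Yes. The HbA1c criterion removes only diabetes that is uncontrolled above 9. The separate exclusion of co-morbid conditions that would interfere includes "thyroid disorders, endocrine diseases" but does not name diabetes. Reading it as a bar on all diabetes would make the HbA1c criterion and the diabetes subgroup pointless.

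**2. Where is baseline glucose drawn?**

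| Place in protocol | Glucose | Insulin or HOMA-IR |
|---|---|---|
| Schedule of Assessments | Screening, Day 84 | Day 1, Day 84 |
| Laboratory cost table | Screening, Day 84 | Baseline, Day 84 |
| Day 1 and Day 84 visit lists | Day 1, Day 84 | Insulin not named (lists end in etc.) |
| Laboratory Investigations, baseline tests | Glucose not named; screening results carried over | Insulin not named |

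The budget funds two glucose tests, not three: Rs 50 × 2 × 204 = Rs 20,400, the table's figure. The table works on 204 = 170 × 1.2, although the column is headed 170. Insulin also reproduces: 26,000/85 × 2 × 204 = Rs 124,800. At Day 84 the schedule, cost table and visit list all place glucose at the same visit as HOMA-IR or insulin.

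**3. Does split-day pairing matter?** Assume within-person coefficients of variation (CV) of 5–10% for glucose and 20–30% for insulin, and a same-day correlation r of 0 to 0.6.

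- Same-day CV of the index = √(CVg² + CVi² + 2·r·CVg·CVi). Lowest: √(0.05² + 0.20²) = 0.21. Highest: √(0.10² + 0.30² + 2 × 0.6 × 0.10 × 0.30) = 0.37.
- Split-day CV = √(CVg² + CVi²), from 0.21 to √(0.10² + 0.30²) = 0.32.

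Under these assumptions the split adds no material error.

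**4. Dilution.** Let a share p have an index carrying no treatment effect, with variance unchanged. The mean effect kept is 1 − p, and the sample needed rises by 1/(1 − p)². For p = 0.05 these are 0.95 and 1.11; for p = 0.30 they are 0.70 and 2.04. The protocol gives no p.

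**5. Effect on a change score (assumed values).** Use the constant 405 for mg/dl and microU/ml, glucose of 120 mg/dl at both visits, and measured insulin falling from 60 to 40 microU/ml.

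- Change in index = 120 × (60 − 40)/405 = 5.9.
- Five such people among 72 in one arm move that arm's mean change by 5 × 5.93/72 = 0.41.
- Spread evenly over the arms, such changes cancel in the difference between arms and leave added variance.

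**The case against.** **The analysis set is a matter for the SAP.** The protocol promises a detailed SAP before unblinding, with covariate adjustment and a diabetes subgroup, and a restriction could sit there. This stands in part: nothing here shows that the SAP lacks one. But the protocol defines both outcomes without restriction, and a SAP cannot settle which blood is drawn when or recover a sample never taken.

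**Randomisation protects the comparison.** Allocation is 1:1 and double-blind, so insulin users are balanced on average. This stands, and it is why the harm is noise and dilution, not systematic bias.

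**A stable dose contributes little.** A reader might set an index of 120 × 60/405 = 17.8 against 120 × 12/405 = 3.6 and conclude that five insulin users among 72 inflate the arm mean by 5 × 14.2/72 ≈ 1.0, or 28%. That is a shift in level with every user placed in one arm. The outcome is change, and a person with the same high value at both visits adds nothing to it. Nor does the protocol plan insulin dose changes; it says that therapy continues and that treatment may be added. How much injected insulin the assay would register is not described either.

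**The timing conflict is small.** A reader might infer that the baseline index is mistimed for everyone else. The documents do not support that: the Day 1 list allows a same-day pair, and on the other reading both values are expected before treatment and less than 2 days apart. Post-enrolment procedures take place at one hospital, so sites diverging from one another is not the worry. The open-ended visit lists may also be meant to cover insulin. What remains is a contradiction to reconcile.

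**Conclusion.** The point holds in limited form. The eligibility and concomitant-therapy rules let insulin-treated participants into two outcomes that cannot be read as insulin resistance in them. The expected consequence is added variance and a diluted effect, with possible chance imbalance between arms. Its size depends on the unstated share of insulin users; over an assumed 5–30%, 95% to 70% of the mean effect remains. This rests on the assay registering at least some injected insulin.

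The baseline glucose conflict is real but minor for precision. Its more practical side is that no visit list names the insulin sample. Neither matter touches the primary LDL cholesterol outcome. The repair is worth making because it is cheap and uses information that is already collected.

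**What to change.** 1. **Secondary Outcome measures:** state that change in fasting insulin and HOMA-IR are analysed in participants not using insulin at baseline.
2. **Insulin started after randomisation:** handle it by a sensitivity analysis, not by exclusion. Removing people for a post-randomisation event that treatment could influence would run against the protocol's intention-to-treat principle. The concomitant therapy record already holds the drug and dates.
3. **Sampling:** reconcile the Schedule of Assessments, the Day 1 and Day 84 visit lists, Laboratory Investigations and the laboratory cost table, so that glucose and insulin for HOMA-IR come from the same fasting sample on Day 1 and on Day 84. Name insulin in those lists.

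**Cost:** a slightly smaller denominator for two secondary outcomes and at most one extra glucose test per participant, 170 × Rs 50 = Rs 8,500 (Rs 10,200 on the cost table's base of 204). No treatment rule changes.
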